## 3. Description and Rationale of the PACO Study

### 3.1. Pilot Phase of PACO Study

The school-based intervention (including both the intervention content and process evaluation tools) was piloted in 2018. The intervention was initially designed by research staff and subsequently reviewed by research experts and three PE teachers. The intervention was then piloted to ensure its feasibility and was implemented within PE classes in 14 3rd grade adolescents from one school in Granada, Spain. Some improvements, such as the number of activities and the session organization were modified based on observations by research staff, an interview with a PE teacher, and a focus-group with adolescents performed after the pilot intervention.

### 3.2. Description of the Intervention in the PACO Study

The PACO study comprises a school-based cycling intervention that will aim to promote cycling to and from school and to increase PA levels, while addressing relevant factors within the PE curriculum for secondary education. It is based on the intervention strategies proposed by the Active Living by Design Community Action Model framework [52] including: *preparation* through developing an intentional intervention, *promotion* through educating and encouraging participants on adopting cycling behaviours, and *programs* through organizing activities to engage the participants. These three strategies have been the most commonly used in published ACS interventions [22,25].

The research staff designed the intervention based on previous experience with other school-based ACS interventions and evidence on effective school-based strategies to promote ACS [22,25] and, particularly, cycling to school [53,54]. A main priority was to design a feasible school-based intervention to be implemented within the PE sessions. The intervention objectives, content, components (i.e., knowledge, skills, and attitudes), and the methodological approach are based on the current Spanish national educational law for compulsory secondary education [55]. The contents of the four intervention sessions have been published [56] and are available online (http://profith.ugr.es/pages/investigacion/recursos/manualbici/) to be used by any teacher. Consistent with the RE-AIM framework [42], if the intervention proves effective, it might contribute to promote the adoption and further scale up of this intervention.

The PACO study intervention is based in the Bikeability methodology [57], as a cycle training intervention to gain practical skills and understand how to cycle on roads. Given that the intervention objective is to promote cycling to school, the intervention components and contents are focused on: (a) *knowledge* about road safety rules, cycling safety equipment, cycling hand signals, and the benefits of cycling as a mode of commuting; (b) *skills* related to cycling in a traffic-free and on-road in urban context, and (c) *attitudes* related to awareness, confidence, enjoyment, and usefulness of cycling.

The 7 h intervention has four sessions that will be implemented during PE sessions over a period of one month (1 weekly session). An expert teacher in cycling in an urban context will lead all the intervention sessions, and the PE teachers will attend to learn and support the sessions. The sessions are described below (see Figure 4):

(1) Theoretical session (60 min—first week): theoretical session in the classroom to provide the participants a first step in the concept of cycling as a mode of commuting in the city. The content will include: awareness about the benefits and usefulness of cycling as a mode of commuting, knowledge about road safety rules for cycling, knowledge about cycling safety equipment for both the rider and the bicycle, and cycling hand signals in urban context.

(2) Closed circuit session (120 min—second week): practical session on the school grounds to learn or improve the fundamental cycling skills needed to ride the bicycle safely. The participants will practice how to fit the helmet and check the bicycle before cycling, as well as the fundamental cycling skills through 10 activities and a cycling circuit. The contents will include: correct helmet fitting, bicycle safety check before the ride, and the fundamental cycling skills of starting off and pedalling, breaking safely, changing gears, and hand signals to change directions.

(3) Urban circuit session (120 min—third week): practical session in urban context on-road traffic to transfer the previously learnt cycling knowledge and skills. The participants will learn advanced cycling skills on-road and will use the previously learnt cycling skills in new, uncertain, and modifiable on-road situations exposed to urban traffic. The content will include: starting from side of road (curb), stopping on side of road (kerb), overtaking a parked or slower-moving vehicle, lane changing, turning right and left, and crossing a roundabout.

(4) Bicycle´s party (120 min—fourth week): theoretical and practical session on the school grounds to strengthen previous learning. The participants will become teachers of their younger peers from 1st grade of secondary education. The content will include three activities based on knowledge and fundamental cycling skills learnt in the previous sessions about on-road cycling practice: “fine tuning”, “handling” and “driving”. “Fine tuning” activity will include bike fitting, correct helmet fitting and parking, basic bicycle check, and basic rules of cycling and signalling. “Handling” activity will be a basic cycling skills circuit with tasks including looking back, extending the arm for the right/left turn, looking back and extending the arm for the right/left turn, zig-zag and stopping area, with possible variations (e.g., making the circuit with one hand, changing gears, and grabbing the hand of a partner). “Driving” activity will include exercises to develop the main skills required for road traffic: left and right signalling, reduction/stop signalling, obstacle warning and looking back signalling. The activities will be displayed in a circuit and the younger students will perform these consecutively.

Participating schools will provide the required material for the intervention sessions (i.e., signalling objects -cones and hoops- to build the circuits). Each adolescent participant will need to have access to a bicycle and helmet in the second, third, and fourth session and a reflective vest the third session. Based on previous research experience and previous technical reports [16], it may be unrealistic to expect all participants to own and bring bicycles to the secondary school. Consequently, some alternative strategies will be considered for implementation of the PACO study intervention: (a) in the second and fourth session, half of the students will perform the activities first, followed by the other half, (b) since cycle training session schedules are different for each class group, students in one class could lend their bicycles to students in another class, (c) some high schools have their own bicycles that are offered freely to the students, and d) local traffic or commuting organizations can be asked to lend the bicycles for the intervention.

Regarding the methodology, the sessions will promote the student´s participation and the language used for communication will be inclusive and adapted to them. Active participation of the students will be promoted through questions, encouraging dialogue, and providing meaningful individual and group feedback. The urban circuit (third session) will be supported by expert cycling instructors and school teachers, to accomplish the ratio of 2 adults (i.e., one cycling instructor and one schoolteacher) per 10 participants.

## 4. Measurement Procedures and Outcome Measures

This study will gather data using questionnaires, anthropometry measurements, accelerometry, and the Global Positioning System (GPS).

### 4.1. PACO Study Assessment Protocol

In the PACO study, assessments will be performed at baseline (before the 4-week intervention period) and immediately after the intervention period for both intervention and control groups (see Figure 5). A further detailed description has been published [58]. All measurements will be completed at participant’s school by trained research staff during 3 assessment sessions conducted over 9 days both at baseline and after the intervention period:Assessment session 1 (1 h): this session will include anthropometry assessment at an indoor sport facility. During this session, participants will receive their accelerometer and the activity diary as well as a family questionnaire for their parents to complete at home.Assessment session 2 (1 h): participants will receive their GPS unit and corresponding instructions.Assessment session 3 (1 h): during this classroom-based session, participants will return their accelerometer, the activity diary, the GPS unit, and the completed family questionnaire. During this session, participants will also complete a student questionnaire online or on paper. The questionnaires will be subsequently read using DataScan [59] to guarantee an objective process.

### 4.2. Outcome Measures

The primary outcomes are adolescent´s behaviours (i.e., cycling to school, ACS–walking and cycling, and PA). Other variables include a range of individual, interpersonal, and environmental factors that are related to ACS (see Table 1), and they will be potential mediators or covariates in the statistical analysis. All the questionnaires self-reported by students will be compiled in a global Student questionnaire; and all the questionnaires self-reported by families will be compiled in a global Family questionnaire.

#### 4.2.1. Primary Outcomes

(1) Cycling and active commuting to and from school

The Student questionnaire includes the *Mode and Frequency of Commuting To and From School Questionnaire* which has been previously validated with accelerometer in Spanish children and adolescents [60] and its reliability has been recently assessed [61]. It is a 4-item self-report instrument designed to evaluate the usual mode and weekly frequency of mode of commuting in children and adolescents. The four questions included in the questionnaire are: (1) *How do you usually get to school?*; (2) *How do you usually get home from school?*; (3) *How did you get to school each day?*; and (4) *How did you get home from school each day?*; answer options: (a) *walk*; (b) *bicycle*; (c) *car;* (d) *motorcycle*; (e) *bus*; (f) *public bus*; (g) *metro/train/tram*; or (h) *other* (the mode description was required). The final variable to analyse will be the percentage of usual cycling and active modes of commuting to and from school, and the weekly number of cycling and active travels to and from school. Furthermore, two relevant questions closely related to the active commuting behaviour will be completed by the participants: the distance and time to school. The questions are: (1) *How far do you live from school?;* answer options: (a) *<0.5 km;* (b) *0.5 km to <1 km;* (c) *1 km to <2 km;* (d) *2 km to <3 km;* (e) *3 km to <5 km;* and (f) *5 km or more*; and (2) *How long does it take to get to the school since you leave your house?*; answer options: (a) *<15 min;* (b) *15 min to <30 min;* (c) *30 min to <60 min;* and (d) *60 min or more*. Travel time will be classified as “<15 min” if they commuted to school taking less than 15 min and “≥15 min” if they were commuted to school taking 15 min or more [69].

In addition, the parents will complete the family commuting-to-school behaviour questionnaire at home, self-reporting their children´s usual mode of commuting to and from school and the distance and the time to school, using similar questions to those previously reported by the adolescents. A recent study has concluded a very good reliability between children and parents’ self-reports about the mode of commuting to and from school, distance, and time to school in children and adolescents [62].

(2) Physical Activity

PA will be measured objectively with a triaxial accelerometer (Actigraph wGT3X-BT, Pensacola, FL, USA) for 7 consecutive days, during waking time. Adolescents will be instructed to use an accelerometer attached to the waist on the right side of the body. Additionally, they will be instructed in the care of the device and it will be removed during water activities and sleeping time during night. Students will also complete an activity diary to record when the accelerometer is removed, the time when they wake up and go to sleep, as well as, the time when they go out from home to school. The Actilife software (Actigraph, v.6, Pensacola, FL, USA) will be used both for the initial configuration before the evaluations and for the data dump registered during the evaluation week. Accelerometers should be programmed with a frequency of 90 Hz and an epoch length of 15 s according to the recommendations for the sample of this study (adolescents) [70]. The final variables to analyse will be the daily minutes of light, moderate, vigorous, moderate to vigorous, and total PA.

In addition, we will also extract accelerometer data from specific times of the day for each participant, calculating the PA during commuting from home to school, commuting from school to home, in-school and out-of-school hours. Participants will carry a GPS (model Q STARZ BT-Q1000XT -Q STARZ International Co., Ltd. Taipei, Taiwan) on the left side of the body on the same belt of their accelerometer during the last two consecutive week days carrying the accelerometer.

Moreover, the PA will be self-reported through the questionnaire Youth Activity Profile, which provides a simple, low-cost, and educationally sound method that have already been calibrated and validated to accurately estimate children’s MVPA and sedentary behaviour at the group level [71,72]. A Spanish version of the Youth Activity Profile questionnaire was elaborated using a back-translation process and it has been shown to be a feasible and reliable questionnaire in Spanish adolescents [63]. The Youth Activity Profile questionnaire includes a total of 19 items, including 4 general items and 15 specific items divided into three sections: (1) activity at school, (2) activity out of school, and (3) sedentary habits. The final variables to analyse will be an average score ranging from 1 to 5 (lowest to highest) about the PA at school and PA out-of-school.

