## Abstract

This manuscript describes the rationale and protocol of a school-based randomized controlled trial called “Cycling and Walk to School” (PACO, by its Spanish acronym) that aims to promote cycling to and from school and physical activity (PA) in adolescents. This study will examine the effects of this intervention in cycling and active commuting to and from school (ACS), PA and several ACS-related factors based on self-determination theory (SDT) and a social-ecological model (SEM). A total of 360 adolescents attending six high schools (three experimental and three control) from three Spanish cities will participate in this randomized controlled trial. The intervention (four cycling sessions; 1–2 h per session, one session per week) will be conducted by the research staff; the control group will continue their usual activities. PA levels will be measured by accelerometers, whereas ACS and the other study variables will be self-reported using questionnaires at baseline and post-intervention. The primary outcomes will be: rates of cycling to school, ACS and PA levels. In addition, SDT-related variables and individual, interpersonal, community, and environment variables relevant to ACS will be based on SEM. The findings will provide a comprehensive understanding of the short-term effects of this school-based intervention on cycling to school behaviour, ACS and PA levels in Spanish adolescents.

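### Cycling to school, a near-zero primary outcome, rests on self-report after an unblinded cycling course, and the GPS and accelerometer data on the same trips have no stated role in checking travel mode

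*Protocol article*

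**What the plan says.** The Abstract states that "ACS and the other study variables will be self-reported using questionnaires at baseline and post-intervention". Section 4.2.1 defines the analysed commuting variable: "The final variable to analyse will be the percentage of usual cycling and active modes of commuting to and from school", together with weekly numbers of cycling and active trips. Both come from a four-item pupil questionnaire: items 1 and 2 ask the usual mode, items 3 and 4 the mode on each day. The instrument is described as "previously validated with accelerometer in Spanish children and adolescents", and its reliability is also cited.

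Section 4.1 places follow-up "immediately after the intervention period for both intervention and control groups". The pupil questionnaire is filled in, online or on paper, in the classroom session at which the accelerometer and GPS unit are handed back. Section 3.2 lists attitudes, including the usefulness of cycling, among the course's targets.

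There are two other sources on travel mode. First, "the parents will complete the family commuting-to-school behaviour questionnaire at home", which covers the child's usual mode; no rule says how it enters the analysed variable. Second, pupils carry a GPS unit "on the left side of the body on the same belt of their accelerometer during the last two consecutive week days carrying the accelerometer". Section 4.2.1 describes the GPS beside the extraction of activity during commuting, and Section 4.2.2, item (11), uses it for the real home–school route and distance. No section uses it to classify or check mode.

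**The concern.** Pupils cannot be unaware that they have been taught to cycle, so any wish to give the hoped-for answer falls mainly on the intervention arm and biases the effect upward. Earlier validation and reliability work shows how the questionnaire performs in general. It does not show that reporting stays equal between arms after an intervention that promotes one of the answers. Because cycling is so rare, a small difference in reporting can be as large as the effect the trial hopes to see. The trial already collects device data on some of the same trips that could show whether this happened, yet the article does not plan to use them for that purpose.

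**Working it through.** The plan gives no figure for this risk, so there is none to reproduce. The sample-size statement in Section 2.3.3 concerns physical activity and does not bear on it.

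**Inputs from the article.** 180 pupils per arm (Section 2.2); background cycling 0.3% to under 2%, walking about 50% (Section 1.1); significance level 0.05 (Section 6); pupils as the units of analysis (Section 2.1); up to 50% loss (Section 2.3.3).

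**Assumptions.** Equal true cycling in both arms; a fraction o of intervention non-cyclists answers 'bicycle'; no over-reporting among controls. The values of o are illustrative. Fisher's exact test and the uncorrected chi-square test stand in for the planned ANCOVA; like it, they ignore school clustering.

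**Step 1. Expected cyclists per arm.** 180 × 0.003 = 0.54; 180 × 0.02 = 3.6.

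**Step 2. Smallest intervention count with two-sided p<0.05, 180 per arm.**

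| Control cyclists | Chi-square: count (excess) | Fisher: count (excess) |
|---|---|---|
| 0 | 4 (4), p = 0.044 | 6 (6), p = 0.030 |
| 1 | 7 (6), p = 0.032 | 8 (7), p = 0.037 |
| 2 | 9 (7), p = 0.032 | 10 (8), p = 0.036 |
| 3 | 10 (7), p = 0.048 | 12 (9), p = 0.032 |
| 4 | 12 (8), p = 0.041 | 13 (9), p = 0.044 |

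The excess is 4 to 9 answers: 4/180 = 2.2% to 9/180 = 5.0% of the arm. The counts are nearly the same at 150 or 90 per arm.

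**Step 3. Chance of a false significant benefit.** The apparent intervention rate is p1 = p0 + o(1 − p0). At p0 = 0.01 and o = 0.03, p1 = 0.01 + 0.03 × 0.99 = 0.0397, so 7.1 against 1.8 expected pupils. Summing exact binomial probabilities over all significant outcomes that favour the intervention, 180 per arm:

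| Background | o = 0 (chi-square / Fisher) | o = 3% | o = 5% |
|---|---|---|---|
| 0.3% | 0.1% / 0.0% | 63% / 40% | 90% / 81% |
| 1% | 1.8% / 0.2% | 43% / 30% | 77% / 67% |
| 2% | 2.2% / 0.8% | 33% / 23% | 64% / 53% |

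At 90 per arm, after the 50% loss the plan allows for, o = 3% gives 27% / 6% at 0.3% background and 17% / 7% at 2%. The problem shrinks but remains.

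**Step 4. Active commuting overall.** With 90 of 180 control pupils commuting actively, the intervention arm needs 109 (chi-square, p = 0.044) or 110 (Fisher, p = 0.044), an excess of 19 or 20. At a 50.3% background, 5% over-reporting gives a false significant benefit in about 7% of trials by chi-square, against 2.6% with none. A walker who answers 'bicycle' does not change this outcome at all.

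**Step 5. What GPS could check.** Two weekdays × two trips × 360 pupils = 1,440 trips at follow-up, or 720 with 50% loss. This assumes that the daily-mode items cover the GPS days; the timing in Section 4.1 makes that likely, but the article does not say so outright.

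**The case against.** **The article is condensed.** Section 4.1 refers to a separate published description of the assessments, which is not shown. That stands: 'no role' means no role stated here. But Sections 4.2.1 and 4.2.2 do say what the outcome variable is and what the GPS is for, and checking mode is in neither place.

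**Over-reporting rates are assumed, and modest ones need not produce significance.** This also stands. At 1% background, 2% and 3% over-reporting give rounded counts of 5 v 2 and 7 v 2; neither is significant (Fisher p = 0.45 and 0.17; chi-square p = 0.25 and 0.09). The risk is a raised false-positive rate, not a settled result.

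**There is a second report.** Parents answer at home, and Section 7 lists lack of family involvement in the intervention as a limitation, so they are under less pressure than pupils. They may still know of the programme, and their report has no stated place in the analysis. It is a useful but imperfect check.

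**Stronger readings that a reader might infer.** One is that those who run the course also supervise the outcome questionnaire. The Abstract says that the sessions "will be conducted by the research staff; the control group will continue their usual activities", and Section 4.1 that "All measurements will be completed at participant’s school by trained research staff". But Section 3.2 has an expert cycling teacher lead every session, and nothing says that this person supervises the questionnaire. Another is that every primary outcome is equally exposed. Step 4 shows that active commuting overall is not, and the main physical activity measure is the accelerometer. A third is to set inflated odds ratios for cycling against the 1.5 in Section 2.3.3; that figure is tied to physical activity and is no benchmark for cycling.

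**Conclusion.** The concern holds for cycling to school. This primary outcome is analysed only from pupil self-report, taken immediately after an unblinded course that encourages the behaviour. At the article's background rates an excess of about 4 to 9 answers is enough for p<0.05. Under an assumed 3% over-reporting with 180 per arm, a false significant benefit arises in 23–40% (Fisher) or 33–63% (chi-square) of trials, against about 2% or less with none.

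These figures rest on pupil-level tests; an analysis that respected the three schools per arm would need a larger excess. The article does not show that pupils will over-report. It leaves no stated means of finding out, although relevant data are collected in both arms. This is a worthwhile, inexpensive improvement and not a fatal flaw.

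**What to change.** Add to Section 4.2.1:

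- On the two GPS weekdays, each school trip is classed as walking, cycling, motorised or unclassifiable from GPS speed and accelerometer data, by an analyst unaware of group.
- The classification is compared with questionnaire items 3 and 4 for the same days. Agreement is reported by arm, at least for every trip reported as cycling.
- The group effect on GPS-classified cycling trips is reported as a named, supportive sensitivity analysis, alongside the parent report of usual mode.

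The GPS result should not act as a veto on the primary conclusion. With 90 usable pupils per arm, a true rise from 1% to 2% would fail to show more cyclists in the intervention arm about 41% of the time (24% for 1% to 3%). With no effect it would still point that way about 34% of the time. Two days also cannot verify usual mode.

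The cost is mainly analysis time, since the devices are already worn in both arms. The check covers only two weekdays and pupils with usable GPS data, and some trips, such as bicycle against slow urban traffic, may not be classifiable. The number unclassified should be reported by arm.
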